## Abstract

**Background:**

Mild cognitive impairment (MCI) is a condition characterized by memory problems that are more severe than the normal cognitive changes due to aging, but less severe than dementia. Reduced working memory (WM) is regarded as one of the core symptoms of an MCI condition. Recent studies have indicated that WM can be improved through computer-based training. The objective of this study is to evaluate if WM training is effective in improving cognitive function in elderly patients with MCI, and if cognitive training induces structural changes in the white and gray matter of the brain, as assessed by structural MRI.

**Methods/Designs:**

The proposed study is a blinded, randomized, controlled trail that will include 90 elderly patients diagnosed with MCI at a hospital-based memory clinic. The participants will be randomized to either a training program or a placebo version of the program. The intervention is computerized WM training performed for 45 minutes of 25 sessions over 5 weeks. The placebo version is identical in duration but is non-adaptive in the difficulty level of the tasks. Neuropsychological assessment and structural MRI will be performed before and 1 month after training, and at a 5-month folllow-up.

**Discussion:**

If computer-based training results in positive changes to memory functions in patients with MCI this may represent a new, cost-effective treatment for MCI. Secondly, evaluation of any training-induced structural changes to gray or white matter will improve the current understanding of the mechanisms behind effective cognitive interventions in patients with MCI.

**Trial registration:**

ClinicalTrials.gov NCT01991405. November 18, 2013.

## Background

Mild cognitive impairment (MCI) is a clinical condition characterized of a reduction in memory and/or other cognitive processes that are insufficiently severe to be diagnosed as dementia, but are more pronounced than the cognitive decline associated with normal aging. In Norway, MCI and dementia represent major health concerns, which will be even more pronounced in the future because of the demographic shift that is resulting in an increased number of elderly citizens. The economic burden of these disorders both for the individual and for society is a heavy one [1,2]. Currently, no treatment is available for enhancing memory function or preventing further decline in patients with MCI. Impairment of memory and learning, including the working memory (WM) capacity, characterizes an MCI condition [3].

WM is a theoretical construct referring to the structures and processes associated with our ability to keep information in mind, while we actively use and respond to the information [4,5]. Individuals with WM deficits have trouble remembering information even for a few seconds, find it difficult to keep track of what they are doing as they work, or forget what they are supposed to retrieve when sent on an errand [6]. Previously, a person’s WM capacity was presumed to be constant and unmodifiable by stimulation or other external factors. Recently, the 'neuroplasticity paradigm' has gained support, and a growing body of research has focused on the brain’s modification capabilities. The notion that mentally stimulating activities may affect cognitive processes, including memory, has also been linked to a 'use it or lose it' hypothesis [7].

Different interventions have been developed to try to enhance or preserve cognitive function [8]. Strategic interventions (by which an individual learns strategies to circumvent and compensate for the cognitive deficits) may be difficult for patients with MCI patients because of their memory problems. We use the definition suggested by Jolles and Crone [9] of cognitive training as the process of improving cognitive functioning by means of practice and/or intentional instruction. The intervention method in this study can be classified as a process-based approach, which involves repeated performance (that is, practice) of demanding (WM) tasks, for which an underlying change in neural correlates is hypothesized [9,10]. WM capacity is associated with the organization of the white matter tracts that constitute the network between the parietal and the frontal lobes [11]. This assumption has been supported by the finding that adaptive WM training causes structural changes of the nerve tracts in the brain [12-14]. It is plausible to expect that performance gain in WM would improve various everyday activities that place high demands on WM capacity [9,15-17].

Positive effects of WM training have been reported in diverse clinical groups, including children with attention deficit hyperactivity disorder (AD/HD), as well as preschool children and youths born preterm with very low birth weight [18-32]. Reviews have reported moderate to large beneficial effects of cognitive exercises on memory-related outcomes [8,10,33]. Enhancing the function in specific domains by training the impaired skill(s) demonstrate the greatest overall effect on functioning compared with non-training methods such as memory strategies and compensatory strategies in patients with Alzheimer’s disease [8]. Several studies have reported improved performance on tasks included in the intervention (trained tasks) as well as improvement on non-trained WM tasks and other cognitive tasks that require spatial skills and involve complex problem-solving skills. However, there is a lack of studies on effective training interventions for MCI patients, and the few randomized controlled trials (RCTs) that exist have shown divergent results [16,33,34]. In addition, the existing studies have the limitations of non-standardized intervention methods and low statistical power, rendering conclusions on these matters challenging. It is therefore of great importance to perform RCTs investigating the effects of specific cognitive interventions in elderly patients with MCI who are at high risk of developing dementia. In addition, the proposed study seeks to investigate individual differences in training outcome and its relation to dementia biomarkers such as tau, phospho-tau, and β-amyloid proteins as well as candidate genes such as *APOE* and *LMX1A*. A recent study by Bellander *et al*. [35] indicates that certain combinations of the different alleles of the *LMX1A* gene might predict those healthy adults most likely to benefit from WM training. This gene is involved in both development and maintenance of dopamine-producing neurons, which are related to WM function [36-40]. If this applies to the MCI group, such a biomarker could be a marker for the effects of the intervention and thereby correlate with the feasibility of this particular intervention. This article describes a study that it aimed to increase knowledge of the neuropsychological status in patients with MCI, as well as the feasibility and possible effects of a cognitive training intervention.

## Methods/Design

### Objectives

The primary objective of this blinded RCT is to evaluate the hypothesis that standardized computer-based WM training is effective in improving WM capacity over time in patients diagnosed with MCI. Second, we want to assess whether computer-based adaptive WM training in patients with MCI has transfer effects to other cognitive functions, including memory, attention, and executive functions, as well as activities of daily living, measured by a battery of neuropsychological tests. Third, any effects of WM training on the structural changes in white and gray matter of the brain will be investigated, measured by multimodal magnetic resonance imaging. Finally, possible genetic biomarkers (*LMX1A* and *APOE* genotypes) related to a positive effect or lack of effect of the training will be examined.

Study approval was given by the Norwegian regional committee for medical and health research ethics, south-eastern region (reference number 2013/410/REK Sør-øst). The study will be reported in accordance with both the CONSORT statement and the CONSORT statement for non-pharmacological interventions [41,42].

### Participants

In total, 90 patients diagnosed with MCI recruited from memory clinics at Sørlandet Hospital, Arendal, The Hospital of Telemark, and Oslo University Hospital will be included in the study. The patients will undergo standard medical examination and neuropsychological testing to ensure correct diagnosis of MCI. Informed consent will be obtained from each participant.

### Inclusion and exclusion criteria

Patients who meet the Peterson diagnostic criteria of MCI [2]: 1) memory problems, preferably confirmed by an informant, 2) memory impairment in accordance with age and education, 3) preserved general cognitive function, 4) intact activities of daily living, and (5) absence of dementia (in accordance with the ICD-10/DMS-IV criteria). Patients who have had head trauma with post-traumatic loss of consciousness for at least 30 minutes during their lifespan, or who have loss of senses (blindness, deafness) or photosensitive epilepsy or who are unsuitable for magnetic resonance imaging because of implanted metal foreign bodies or severe claustrophobia will be excluded from the study.

### Outcome measures and assessment procedures

Baseline assessment will be completed prior to randomization and the first intervention session.

### Neuropsychological assessment

The neuropsychological/cognitive evaluation includes the administration of several commonly used measures (tests, interview, and questionnaires) of cognitive abilities and daily functions. Measures of the patient's cognitive status (intelligence, memory, processing speed, attention, and executive functions) will include a wide range of standardized neuropsychological tests, as well as tests assessing prefrontal functions, as these may mediate WM decline [43]. Measures are administered as a combination of paper-and-pencil tests and a computer-administered task. The sensitivity and specificity of the assessment methods have been described previously [44,45]. To correct for learning effects on repeated tests, alternative test versions or forms will be used when possible. The selected neuropsychological tests and assessed functions is described in Table 1.

**Table 1 T1:** Summary of assessed cognitive functions and tests

**Function:**	**Tests:**
General cognitive ability (IQ)	WAIS-IV
Auditory and visual WM	Digit Span, Spatial Span/Span Board and Letter-Number Sequencing, PASAT
Verbal and visual learning, immediate and delayed memory	WMS-III, CVLT-II
Attention and executive functions	D-KEFS subtests including: Trails 1 to 5, Color Word Interference, Tower, Verbal fluency, Design fluency. Supplemental test: Iowa Gambling Task

### Interview and questionnaires

The following interviews and questionnaires will be used.

• Vineland Adaptive Behavior Scales, second edition (interview). This structured interview measures adaptive abilities in three broad domains: communication, activities of daily living, and social skills.

• Behavior Rating Inventory of Executive Functions Adult version (BRIEF-A). This questionnaire measures nine domains of executive functions (inhibition, shifting, emotional control, self monitoring, initiating, WM, planning/organizing, task monitoring, and organization of materials) through a self-reported and an informant version.

• Behavioral assessment of the Dysexecutive Syndrome Questionnaire (DEX). Assesses problems in executive function through a self-report and an informant version.

### Magnetic resonance brain imaging

The patients will undergo brain MRI scanning at baseline and at 1 and 4 months post-training, using an optimized protocol. Following a pilot scan, a three-dimensional (3D) magnetization-prepared rapid gradient echo (MP-RAGE) scan will be performed (sagittal, echo time 3.47, repetition time 2400, TI 1000, flip angle (FA) 8 degrees, 1.2 mm resolution covering the whole brain).

Diffusion tensor imaging (DTI) scan will be performed (axial (non-oblique), 68 slices, field of view = 240 mm, 2.5 mm slices without gap; 2.5 × 2.5 mm in-plane resolution; repetition time9.500, echo time 91, two averages, diffusion (b = 0.1000), 30 diffusion directions. In addition a 3D-T2 space dark fluid (FLAIR) image (sagittal, echo time 335, repetition time 5000, TI 1800, turbo factor 242, 1.2 mm resolution covering the whole brain) and a T2* image (axial TE 25, TR 830, flip angle 20 degrees) will also be acquired during the initial scan for clinical evaluation to exclude microbleeds. Total scanning time for the initial scan will be close to 30 minutes. The follow-up scans will be under 25 minutes. All scans will be reviewed qualitatively by a radiologist to screen for possible brain lesions or structural abnormalities. By using tract-based spatial statistics (TBSS), the radiologist will measure fractional anisotropy, and mean diffusivity values in central white matter tracts before and after training. Automated morphometry to evaluate cortical thickness, surface area, and total gray and white matter volumes, as well as deep nuclei volumes will be performed.

### Biological/biochemical samples, study biobank, and DNA collection

One oral cotton swab will be collected for genotype analyses for *APOE* and *LMX1A* alleles. DNA will be extracted from saliva collected using an Oragene Self collection Kit (DAN Genoteck, Inc. Ottawa, Ontario, Canada). Genomic DNA will be subjected to Restriction Fragment Length Polymorphism analyses (RFLP-PCR). Approximately 3 ng of genomic DNA for *LMX1A* will be amplified by PCR using the primer LMX-5′: 5′-CTCGCCTCCAGGAA TGGGTGTTGTA-3′and LMX-3′: 5′-GCCACGAGGAACTTGTGAGAGGGTT-3′ with the following conditions: denaturation at 94°C for 5 minutes, followed by 25 cycles at 94°C for 30 seconds, annealing at 64°C for 30 seconds and extending at 72°C for 30 seconds. Then 15 μl of the amplification PCR products will be digested directly by 2.5 U of the restriction enzyme *Msl*I (R0571S, New England Biolabs, Beverly, MA, USA) for 2 hours at 37°C. The digested PCR products will then be analyzed on 4% agarose gel, and visualized using GelGreen™ Nucleic Acid Gel Stain (89139–144, Biotium, Hayward, CA, USA).

### Primary outcome measure

Primary outcome measure is the spatial span board task from the Wechsler Memory Scale, third edition (WMS-III).

### Secondary outcome measures

Secondary outcome measureszare the structural MRI changes, the results on neuropsychological test measuring verbal and visual learning and memory, and the response pattern on the questionnaires.

#### Intervention

The intervention method is classified as an adaptive, intensive, and standardized computerized WM training program (Cogmed®), developed by Professor T. Klingberg at the Karolinska Institute, Stockholm, Sweden [29,46]. Both the adaptive and the 'placebo' training groups will use the program approximately 30 to 40 minutes a day, 5 days a week for 5 weeks. The training is considered 'adaptive', which means that the difficulty level of the tasks increases during the sessions according to the individual level of mastering for each participant, making the patient work at their maximum capacity at all times [46]. This is the core element of the hypothesized effectiveness of the intervention. The placebo group will use a non-adaptive (fixed low-level training) version of the training program. The interface of both the placebo and the training version is identical, but the difficulty level in the placebo version does not increase adaptively as the patient performance improves. The study involves three examinations at the following time points: baseline before training, retesting about 1 month after training completion, and follow-up retesting four months after training completion in order to examine the longer-term effects, see Table 2 for details.

**Table 2 T2:** Assessment measures at baseline and post-intervention evaluations

**Assessment tool**	**Baseline evaluation**	**Post-intervention evaluation**	
		**1: 1 month after training**	**2: 4 months after training**
Medical examination	X		
MR caput	X	X	X
Spinal fluid	X		
DNA sampling	X		
WAIS-IV	X		
WMS-III	X	X	X
Digit span	X	X	X
Spatial span	X	X	X
Letter-Number Sequencing	X	X	X
CVLT-II	X	X	X
D-KEFS	X	X	X
IGT	X		
Vineland	X		X
BRIEF-A	X	X	X
DEX	X	X	X

#### Randomization

Participants in the study are randomly allocated to either the adaptive training group or the non-adaptive (placebo) training group after the baseline assessment. The patients randomized to the placebo group will be offered the adaptive training after the 4-month follow-up examination. The neuropsychologist and radiologist carrying out the assessments are blinded to group adherence.

Both the adaptive and the placebo training groups undergo a 25-session standardized computerized WM training within the same time period (all participants start training/placebo at the same time), differing only in the adaptability of the training. During the training phase, weekly follow-ups by standardized phone interviews are scheduled for all participants regardless of group affiliation. After the initial training phase, the participants are examined at 1 and 4 months after finalizing their training. All participant contact is logged in order to discover potential performance bias. In addition to the research team, the patients are followed by their primary physician, who will tend to all non-trial-related issues.

### Sample size and power calculation

Using pre-training and post-training test scores obtained by Brehmer *et al*. [47], 72 patients are needed for inclusion in the study to obtain a statistical power of 80%. Allowing for a maximum dropout rate of 20%, the number of study subjects needed for inclusion has been set to 90 patients with MCI. Power calculations are based on the primary outcome measure, which is change in WM capacity assessed by neuropsychological tests and behavioral inventories that assess WM and related functions. The statistical power measures will be calculated using Sample Power 2.0.

### Statistical analysis

Performance gain in the assessment scores related to WM function from baseline is the primary outcome of interest. Participants' daily performance on the WM tasks within the program will be aggregated into one *t*-standardized performance score. Weekly performance scores will be used for analysis. A repeated-measure ANOVA will be conducted to investigate performance gain during the training period. One-way ANOVA will be conducted separately for the assessment criterion and transfer tasks and the rating scales of functioning, to examine potential baseline differences between the intervention and the placebo groups. To determine differences in training-related changes, a general linear mixed model with appropriate covariates will be conducted (baseline, post-training, and follow-up), and within-subject factors will be used for the cognitive tasks and assessment data. For all analyses, α levels will be set to 0.05 and effect sizes refer to partial η-square values. With regard to cerebral MRI, the DTI images will be analyzed using the software FSL with [48] to provide information on any changes in white matter microstructure with training. Automated morphometry to evaluate cortical thickness and surface area, total gray and white matter volumes, and deep nuclei volumes will be performed using the freely available FreeSurfer software program, v5.1 [49]. Complete-case analysis will be used where missing data are excluded from the analysis. A fully detailed statistical analysis will be performed before unmasking of the data.

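### The primary outcome is one test in one section and a set of working-memory scores in two others, so the stated 80% power and 5% level are not tied to the named primary outcome.

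*Protocol article*

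**What the plan says.** All references are to the protocol article.

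- **Primary outcome measure:** "Primary outcome measure is the spatial span board task from the Wechsler Memory Scale, third edition (WMS-III"). It does not say which Spatial Span score or which visit.
- **Secondary outcome measures:** structural MRI changes, tests of verbal and visual learning and memory, "and the response pattern on the questionnaires".
- **Sample size and power calculation:** 72 patients for 80% power, raised to 90 for up to 20% dropout. The calculation is said to rest on the "primary outcome measure, which is change in WM capacity assessed by neuropsychological tests and behavioral inventories that assess WM and related functions".
- **Statistical analysis:** "Performance gain in the assessment scores related to WM function from baseline is the primary outcome of interest". The scores are plural and not listed. Training-related change is examined with a general linear mixed model over baseline, post-training and follow-up. "For all analyses, α levels will be set to 0.05".
- **Randomization:** "the participants are examined at 1 and 4 months after finalizing their training". Neither visit is called primary. The Intervention section links the 4-month visit to longer-term effects.
- **Table 1** lists as working-memory tests "Digit Span, Spatial Span/Span Board and Letter-Number Sequencing, PASAT". **Table 2** schedules Digit Span, Spatial Span, Letter-Number Sequencing and BRIEF-A at baseline and at both later visits. PASAT does not appear in Table 2.

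**The concern.** The statement of the primary outcome decides what counts as a positive trial. Here one section gives a single test, and two sections give a set of scores. On the inventories the text contradicts itself directly: they are part of the primary outcome in the sample size section and secondary under Secondary outcome measures.

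Two things are at stake. First, the 80% power is claimed for the multi-measure outcome, so it cannot be read as the power of the Spatial Span comparison. Second, with several candidate scores, two post-training visits, no named contrast and 0.05 throughout, the text does not prevent a favourable result on any one working-memory score at either visit from being presented as meeting the primary objective. In that case the 5% level would not describe the chance of a false claim.

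**Working it through.** **1. The statements side by side**

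| Section | Primary outcome | Inventories |
|---|---|---|
| Primary outcome measure | one test, Spatial Span | not included |
| Secondary outcome measures | – | secondary |
| Sample size and power calculation | several tests and inventories | primary |
| Statistical analysis | working-memory-related scores, unlisted | not stated |

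The last two rows overlap and can be read as one broad definition. That definition still conflicts with the first row, and the inventories are still both primary and secondary.

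**2. The plan's own figures**

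Dropout step: 72 / (1 − 0.20) = 90, which reproduces.

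The 72 can be neither reproduced nor refuted, because the article gives no effect size, SD, sidedness or source test. What it implies can be back-solved. Assume 1:1 allocation (not stated), so 36 per arm, and a two-sided 0.05 test:

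- normal approximation: d = (1.960 + 0.842) × √(2/36) = 2.802 × 0.2357 = 0.66
- two-sample t-test: d = 0.67
- one-sided t-test, for comparison: d = 0.59

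**3. False-positive chance if any one score at either visit may count**

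Inputs: the measures scheduled in Table 2, two post-training visits, and a separate two-sided test at 0.05 for each score and visit. If the tests were independent, the chance of at least one false positive is 1 − 0.95^k:

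- three tests × 2 visits, k = 6: 1 − 0.95^6 = 26%
- adding BRIEF-A working memory by self-report and by informant, k = 10: 1 − 0.95^10 = 40%

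The scores will be correlated. The correlations are not in the documents, so I assumed 0.7 between visits and 0.7, 0.5 or 0.3 between measures, with the product applying across both, and simulated correlated z-tests:

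| Family | 0.7 | 0.5 | 0.3 | Independent |
|---|---|---|---|---|
| 3 tests × 2 visits | 18% | 20% | 22% | 26% |
| 5 measures × 2 visits | 24% | 29% | 33% | 40% |
| Spatial Span alone × 2 visits | 8% | 8% | 8% | 10% |

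**4. Power if the set were kept and corrected**

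Take d = 0.67, 36 per arm and Bonferroni at one visit. For one pre-chosen test, power falls from 80% to 65% with three measures (0.05/3) and to 58% with five (0.05/5). If success on any one measure is enough and all measures carry the 0.67 SD effect, simulation (normal approximation) gives 84% to 92% for three measures and 84% to 95% for five, at between-measure correlations of 0.7 to 0.3.

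**The case against.** The best defence is that only one section is headed Primary outcome measure and that it names one test. The phrases in the other two sections would then be loose descriptions of working-memory gain. The 4-month visit is tied to longer-term effects, and the fifth planned paper covers long-term follow-up, so 1 month looks like the intended primary visit. The mixed model could supply a single group-by-time test per score, in which case testing two visits separately would not arise. The contrast and any multiplicity rule may sit in an analysis plan that is not shown.

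Much of this stands, and it limits the size of the point. The false-positive rates above describe what could be claimed, not what the plan commits to. The defence does not remove the contradiction, because the sample size section expressly calls its multi-measure outcome the primary one and includes inventories that another section makes secondary. An unseen plan can add detail, but the article's own statements would still disagree.

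A reader might infer more than the documents support:

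- **Three rival primary outcomes.** The sample size and analysis wordings overlap. The conflict is one test against a set.
- **Twelve candidate tests.** That count needs PASAT at both visits, and Table 2 does not schedule it. Ten is the count with the two BRIEF-A scores, and including those two is itself a choice.
- **The 80% power would be lost under correction.** This holds for one pre-chosen test under Bonferroni. It does not hold when any one measure suffices and all carry the effect.
- **72 or 90 is the wrong number.** Nothing here shows that. The unnamed test behind the 72 could even have been Spatial Span.

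**Conclusion.** The point holds as an inconsistency in the stated primary outcome, and it should be resolved before unmasking. Confidence in the wording conflict is high, since it can be read directly from four sections. The 80% power is attached to a multi-measure outcome and the 0.05 level to all analyses, so neither is tied to the Spatial Span comparison.

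The size is conditional. If success on any one score at either visit were claimed as primary, with separate per-visit tests, the false-positive chance would be about 18% to 22% for the three scheduled tests and about 24% to 33% for five measures. These ranges rest on the assumed correlations and on the choice of measures. A single overall test of one Spatial Span score would keep its 5% level.

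**What to change.** Let the section Primary outcome measure govern. Name one Spatial Span score and one between-arm contrast in change from baseline, taken from the mixed model at one prespecified visit and tested two-sided at 0.05. The 1-month visit is a reasonable choice because the article assigns the 4-month visit to longer-term effects. Whether it also matches the timing of the scores used for sizing cannot be judged from the documents.

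Class the other working-memory scores, the inventories and the other visit as secondary, and bring the outcome wording in Sample size and power calculation and in Statistical analysis into line.

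Restate the power for that contrast and give the allocation ratio. With 1:1 allocation, 36 analysed per arm give 80% power for a difference of about 0.67 SD of the analysed score, and the sponsor should say whether that difference is plausible.

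The cost is rewording before unmasking, with no new data or visits. The small downside is that other working-memory tests can no longer carry the primary claim. If the sponsor prefers several primary measures, it should list them, state a multiplicity rule and recompute the sample size under that rule.

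### Baseline is significance-tested after randomisation and, on the natural reading, modelled as an outcome level, so precision that baseline adjustment would give at no cost is left unused

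*Protocol article*

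**What the plan says.** The order of events is clear. Under Outcome measures and assessment procedures: "Baseline assessment will be completed prior to randomization and the first intervention session". Under Randomization: "Participants in the study are randomly allocated to either the adaptive training group or the non-adaptive (placebo) training group after the baseline assessment".

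The Statistical analysis section then makes three relevant choices.

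- One-way ANOVAs are run separately on the criterion tasks, the transfer tasks and the rating scales "to examine potential baseline differences between the intervention and the placebo groups".
- The outcome is defined as gain: "Performance gain in the assessment scores related to WM function from baseline is the primary outcome of interest".
- The comparison of training-related change uses "a general linear mixed model with appropriate covariates will be conducted (baseline, post-training, and follow-up), and within-subject factors will be used" for the cognitive and assessment data.

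The section also restricts the analysis to complete cases. It names no covariates and states no use for the ANOVA results.

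**The concern.** Two separate things look wrong.

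First, the baseline tests address a null hypothesis that randomisation has already made true. A significant result is a chance finding, expected in one test in twenty at the stated level ("For all analyses, α levels will be set to 0.05"). A non-significant result does not show that an imbalance is harmless. What matters is how strongly the variable predicts the outcome, and these tests do not measure that.

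Second, if baseline is an outcome level with its own mean in each arm, the model does not use the fact that randomised arms have equal expected baselines. Suppose the arms differ at baseline by a chance amount δ and the training effect is τ. With equal variances, the expected difference in gain given that imbalance is τ + (ρ − 1)δ, because the arm that starts lower tends to regress upwards. Averaged over randomisations the extra term is zero, but in any one trial it adds noise. Adjusting for baseline removes it.

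What is at stake is power on the main between-group comparison, in a trial planned at 80%.

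**Working it through.** **Inputs from the protocol article.** Evaluable patients and power: "72 patients are needed for inclusion in the study to obtain a statistical power of 80" per cent. Dropout 20%, total 90, α 0.05, complete-case analysis.

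**Assumptions, because the article does not give them.** 1:1 allocation (36 per arm), two-sided α, equal variances at baseline and follow-up, a single post-training visit, and a range of ρ.

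**The plan's own figure.** 72/(1 − 0.20) = 90, which matches. The 72 cannot be rebuilt, since no effect size, SD or correlation is stated. Solving backwards at 36 per arm and 80% power gives a standardised effect of 0.66 (normal approximation) or 0.67 (t test).

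**Why the contrast is the raw gain difference.** With free arm means at each visit and complete data, the group-by-time contrast for a visit is the between-arm difference in mean (follow-up − baseline). A covariate that is constant within a patient and enters as a main effect cancels in that subtraction. Adding the baseline score that way would therefore not recover the precision while baseline stays a free outcome level.

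**Variance, in units of σ².**

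- Gain: 2(1 − ρ)
- Baseline-adjusted: 1 − ρ²
- Ratio: (1 − ρ²)/[2(1 − ρ)] = (1 + ρ)/2
- Saving: (1 − ρ)/2

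**Power if the gain analysis has 80%.** Φ(2.80/√ratio − 1.96), with 2.80 = 1.96 + 0.84. The two columns on patient numbers are 72 × ratio and 72/ratio.

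| ρ | Ratio | Saving | Power at 72 | Patients for 80% power | Gain-score patients matched by 72 |
|---|---|---|---|---|---|
| 0.5 | 0.75 | 25% | 90% | 54 | 96 |
| 0.6 | 0.80 | 20% | 88% | 58 | 90 |
| 0.7 | 0.85 | 15% | 86% | 62 | 85 |
| 0.8 | 0.90 | 10% | 84% | 65 | 80 |

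Over a wider range the saving is 35% at ρ = 0.3 and 5% at ρ = 0.9.

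**Check by simulation** (36 per arm, 10,000 trials). The saving was 24.2% at ρ = 0.5 and 8.6% at ρ = 0.8. The small shortfall is the cost of estimating the slope, which multiplies the adjusted variance by about 1 + 1/(72 − 4) = 1.015. This gives 1 − 0.75 × 1.015 = 24% and 1 − 0.90 × 1.015 = 9%. The power figures in the table ignore this cost and are therefore slightly high.

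**Two post-training visits averaged**, with equal correlations. Gain variance is (1 + ρ)/2 + 1 − 2ρ and adjusted variance is (1 + ρ)/2 − ρ². At ρ = 0.5 these are 0.75 and 0.50 (saving 33%). At ρ = 0.8 they are 0.30 and 0.26 (saving 13%).

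**The case against.** The strongest reply is that the article never says the baseline means are free. A model with baseline means constrained equal across arms also has three time levels and would fit the same sentence, and the unnamed covariates leave room for adjustment. A condensed article may leave model terms to an analysis plan, and this one promises detailed statistical work before unblinding. This stands in part: the free-baseline reading is the natural one, given that the outcome is gain and baseline is listed with the two later visits, but it is not certain. The missing covariate list is not itself a fault. The baseline tests, however, are stated outright.

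Three stronger readings are tempting and should be resisted.

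- **Bias or an inflated error rate.** A reader might infer that the gain contrast is invalid. It is not: over randomisations it is unbiased and keeps its type I error. It also matches the stated outcome.
- **Covariates picked by p-value.** Baseline tests next to unnamed covariates leave that route open, but no sentence links the two. It is something to rule out, not something the plan does.
- **A fixed loss of 10% to 25%.** The figure depends on an assumed ρ. It is also a share of the variance of the gain estimate, not of the total benefit that baseline data could bring. Measured against an unadjusted follow-up score, adjustment saves ρ² and gain scores save 1 − 2(1 − ρ). At ρ = 0.5 these are 0.25 and 0, so all of the benefit is lost. At ρ = 0.8 they are 0.64 and 0.60, so about 6% of it is lost.

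One caution about the remedy also stands. Baseline means are equal in expectation among all randomised patients, but not necessarily among completers if dropout differs by arm. Constraining them equal in a complete-case set therefore adds an assumption.

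**Conclusion.** The point holds as a matter of efficiency. The baseline ANOVAs are certain from the text and uninformative. The unadjusted gain contrast is the likely consequence of the model as described. If that reading is right, adjustment would reduce the variance of the effect estimate by 25% to 10% for ρ of 0.5 to 0.8, and by 35% to 5% for 0.3 to 0.9, with equal variances and one post-training visit. The rise in power from 80% to about 90% to 84% rests on the further assumption that the 72 patients were sized on gain scores, which the article does not say. No claim of bias, false-positive inflation or data-driven covariate choice is supported.

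**What to change.** In the Statistical analysis section:

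1. Delete the one-way ANOVAs at baseline and summarise baseline by arm without tests.
2. State that the 1- and 4-month scores are the outcomes of the mixed model, with the baseline score of the same measure as a prespecified covariate whose effect may differ by visit. The Vineland interview has only the 4-month visit (Table 2), so a single-visit version applies there. The outcome can still be described as gain: subtracting baseline from the outcome while keeping it as a covariate leaves the group effect unchanged.
3. As an alternative, keep baseline in the outcome vector with its mean constrained equal across arms, but only if all randomised patients enter the model and not just completers.
4. Say that no baseline test determines the covariates.

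The cost is a few sentences of text and one slope per visit to estimate. The baseline scores are already collected, so no patient, visit or measurement is added.
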